## Materials and Methods

### Population

In this randomized, double blind experimental study, 40 healthy, right-handed participants were enrolled. Hemispheric dominance was assessed through the Edinburgh Handedness Inventory (EHI) (54). The inclusion criteria followed in the study were: (i) age 18–80 years, (ii) absence of visual or auditory disturbances possibly impacting on neuropsychological evaluation, (iii) no previous medical-neurological conditions considered as exclusion criteria for TMS (55), and (iv) no previous psychiatric diseases.

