### Study Design

The participants will be divided into four groups—age, sex, and educational-matched. All the participants will undergo two experimental sessions on a single-day, separated by a break of 45 min, each one including two behavioral tasks based on a modified SRTT paradigm (51–53). Before each session, patients will be subjected to one specific type of cerebellar TBS (Figure 1).

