#### Behavioral Tasks

Serial Reaction Time Task was programmed using SuperLab 5 (Cedrus, San Pedro, CA, USA) and will be administered in a laboratory setting, with constant artificial light and without auditory interference. The hand to be used for the learning task will be randomized, and the contralateral hand subsequently will perform the adaptation task. The participants will seat on a chair in front of a computer screen, where four aligned blue squares will be presented simultaneously. As soon as one of these squares turns red (visual cue), participants are supposed to press as fast as possible the corresponding one of four aligned buttons on a keyboard with the corresponding index, middle, ring, or little finger (D2, D3, D4, and D5, respectively) of the selected hand. Immediately after correct key selection, the visual cue disappeared and the trial ends. After an interval of 200 ms, a new visual cue appeared and a new trial begins. Twelve consecutive trials correspond to the sequence that participants had to learn explicitly. The sequence needs to follow a specific set of rules: (a) the same visual cue does not appear two times successively; (b) each visual cue appears three times; and (c) visual cues are pseudo-randomized. The sequence to be learned is: 2–4–1–3–2–4–3–1–2–4–1–3. The same sequence will be used in each of the four experimental conditions: (1) Motor sequence learning (MSL), in which participants learn the sequence; (2) Adaptation (AD), in which participants are required to execute the learned sequence with the opposite hand; (3) Delayed recall (DR), in which the participants are required to recall the adapted sequence execution after a 45-min break; (4) Re-adaptation (RA), in which the participants have to return back to execute the sequence with the hand that originally learned the sequence (as shown in Figure 1). In MSL, participants will be required to learn the 12-item sequence presented in a 13-consecutive series, each series repeated four times with an inter-series-interval of 1 min. The same procedure will be repeated after 5 min. In AD, participants performed the same 13-consecutive series of 12-item sequences four times, with an inter-series-interval of 1 min with the opposite hand. In DR, participants repeated the AD task after 45 min and following another stimulation protocol (according to group assignment). Finally, in RA, participants will perform the 12-item sequence with the “original” hand in 13-consecutive series, will repeat four times with an inter-series-interval of 1 min. Errors, i.e., wrong key strokes, were counted (accuracy). The time taken to select the correct key will be recorded (response time, RT) (Figure 2).

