### Statistical Analysis

#### Behavioral Task Analysis

Shapiro–Wilk's statistic supported by visual inspection will be used to test the normality of distribution of all variables. Descriptive statistics of collected data will be reported as mean ± SD for continuous variables and as percentage frequencies for categorical variables. To assess data distribution, the variables will be examined by the Kolmogorov-Smirnov (K-S) test. One-way ANOVA will be used to compare differences in baseline values among groups. The effects of two independent variables (groups: specifically, G1 vs. G2; G3 vs. G4; G1 vs. G3; G2 vs. G4; task; MSL, DA, DR, and RA), on both accuracy and RTs of motor skill learning will be evaluated using two-way repeated measures ANOVA.

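### Wrong key strokes are compared across tasks as raw counts, although MSL is run twice (1,248 trials) and AD, DR and RA once each (624)

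*Protocol article*

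**What the plan says.** - **Outcome.** The Behavioral Tasks section states: "Errors, i.e., wrong key strokes, were counted (accuracy"). It gives no denominator. A trial ends only on the correct key, so one trial can contain more than one wrong key stroke.
- **Exposure.** The same section sets a 12-item sequence, presented 13 times in a row and repeated four times, for each run. MSL consists of this procedure and a full repeat of it after 5 minutes. AD, DR and RA each consist of one run.
- **Analysis.** The Behavioral Task Analysis section takes group (G1 vs G2, G3 vs G4, G1 vs G3, G2 vs G4) and task (four levels, with MSL as one of them) as factors. Their effects "on both accuracy and RTs of motor skill learning will be evaluated using two-way repeated measures ANOVA". No rate, transformation or rule for the two MSL runs is given.
- **Sample.** "40 healthy, right-handed participants were enrolled", and "The participants will be divided into four groups", described as "age, sex, and educational-matched". Eligible ages are "age 18–80 years". Group sizes are not stated.

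**The concern.** A repeated measures ANOVA across tasks assumes that the four values per person measure the same quantity on the same footing. A count over 1,248 trials and a count over 624 trials do not. The term affected is the one that matters most. According to the Theta Burst Stimulation section, G1 and G2 receive iTBS and sham in opposite order, and G3 and G4 receive cTBS and sham in opposite order. In those comparisons the active-versus-sham effect therefore appears as group x task. Unequal exposure acts on that term in two ways. It lowers the chance of detecting a real effect, because error-prone people show a larger MSL-to-AD drop in counts even when their error rate is constant. It can also produce an interaction that is not there, when one group simply makes more errors than the other throughout.

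**Working it through.** **Inputs from the protocol article**

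- Trials per run: 12 x 13 x 4 = 624.
- MSL: 2 x 624 = 1,248. AD, DR and RA: 624 each.
- 40 participants in four groups. An equal split, 40 / 4 = 10 per group, is assumed.

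The article gives no error rate, SD, effect size, power or alpha, so there is no stated figure to reproduce. Those inputs are assumptions below.

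**Step 1: artefactual task effect.** Expected count = trials x error rate. At a constant 4% rate:

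- MSL: 1,248 x 0.04 = 49.92
- AD, DR, RA: 624 x 0.04 = 24.96

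The count halves from MSL to AD although the error rate has not changed.

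**Step 2: added person-by-task error.** Take two people with constant rates of 2% and 8%. MSL minus AD in counts is (1,248 - 624) x rate:

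- 624 x 0.02 = 12.48
- 624 x 0.08 = 49.92

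Neither person changes, yet their task differences vary fourfold. The ANOVA removes each person's mean level but not this spread, which goes into the error term for group x task. On rates both differences are zero.

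**Step 3: false interaction.** Let group B exceed group A by the same amount d in every task. The group-by-(MSL minus AD) contrast in counts is 1,248d - 624d = 624d. With 4% against 5%, d = 0.01:

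- MSL: 62.40 - 49.92 = 12.48
- AD: 31.20 - 24.96 = 6.24
- Contrast: 12.48 - 6.24 = 6.24 wrong key strokes

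On rates the contrast is 0.01 - 0.01 = 0.

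**Step 4: size, by simulation.** All scenarios use 10 per group, two groups x four tasks, a 5% level, and both MSL runs summed.

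| Assumptions | Quantity | Counts | Errors per trial |
|---|---|---|---|
| 4% median rate, 25% reduction under active TBS | group x task power | 67-87% | 93-96% |
| 4% median rate, no effect | type I error | 7-8% | excess removed |
| Uniform group difference in rate, no interaction | false group x task interaction | 17-24% | excess removed |
| 3% rate, 30% reduction, overdispersion 0.3 | group x task power | 73% | 86% |
| 3% rate, 30% reduction, overdispersion 0.6 | group x task power | 60% | 79% |
| 3% rate, no effect, overdispersion 0.3 / 0.6 | type I error | 6.5% / 6.5% | 4.7% / 4.2% |

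**Step 5: check that exposure is the cause.** With 624 trials in all four tasks, and the 3% rate and 30% reduction, counts and rates give the same power: 83% at overdispersion 0.3 and 77% at 0.6. Log rates are slightly lower, at 81% and 74%. The loss comes from the unequal denominators, not from using a normal-theory ANOVA on errors.

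**Step 6: RT scale, for comparison.** Group x task power on RT depends on how the effects act:

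| Truth assumed | Raw RT, three scenarios | Log RT |
|---|---|---|
| Proportional effects | 82 / 64 / 45% | about 89% in each |
| Effects additive in milliseconds | 87 / 86 / 76% | 75 / 46 / 32% |

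**The case against.** The article does not say that the two MSL runs are summed. The full plan may average them, use only one, or report a rate, and a journal article may leave that out. This stands as a limit: if one run or the average is used, exposure is equal and the problem disappears. But the article is not silent on the outcome. It defines accuracy as a count, treats MSL as one task level, and describes MSL as containing both runs. Read as written, the MSL count covers 1,248 trials.

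Matching on age, sex and education also makes large group differences in error rate less likely. That weakens the false-interaction risk but does not remove it with about 10 per group, and it does nothing about the spread between people within groups.

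Three stronger readings are tempting and are not supported:

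- **That raw RT will cost power.** A reader might infer this from skewed times and the wide age range. Step 6 shows that logs help if effects are proportional and hurt if they are additive. The article gives no figures to decide between these, and it does not say that RT is analysed untransformed.
- **That the two normality tests contradict each other.** Shapiro-Wilk is named first, and then "To assess data distribution, the variables will be examined by the Kolmogorov-Smirnov (K-S) test". The two are redundant and may disagree on a given sample, but nothing in the text sets one against the other. The lack of a stated consequence is detail that an article may leave to the full plan.
- **That errors need a binomial mixed model scored at first press.** This would replace the stated outcome, since a trial can hold several wrong presses. It would also add almost nothing over simple rates.

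**Conclusion.** The concern holds for the accuracy outcome. Taken per task as written, the counts compare 1,248 trials with 624. The doubling of exposure, and the bias of 624d in the group-by-(MSL minus AD) contrast, follow from the article's own figures. The sizes are scenarios. Across the assumptions tried, power is 60-87% on counts against 79-96% on errors per trial, type I error on counts is about 6.5-8%, and a false interaction occurs in 17-24% of runs under a uniform group difference. They rest on 10 per group, a 3-4% error rate, a 25-30% effect, and summing of both MSL runs.

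Dividing by trials removes the exposure artefact. It does not make group x task free of scale: if error rates truly change across tasks and groups differ proportionally, an interaction in rates can still arise. For RT, the supportable statement is only that group x task depends on the scale chosen.

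**What to change.** In the Behavioral Task Analysis section, define accuracy for analysis as wrong key strokes divided by trials presented in that task: 1,248 for MSL if both runs are used, and 624 for AD, DR and RA. State how the two MSL runs are combined. Keep the raw counts as description. This costs one or two sentences and one division per person and task. The data collected and the ANOVA stay the same, and there is no material downside.

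Optionally, prespecify log RT as a sensitivity analysis alongside the main RT analysis and report both, without replacing the millisecond scale. This costs one extra model, and any disagreement between the two scales has to be reported as such.

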## Discussion

Motor learning is crucial for human behavior, from both a phylogenetic and ontogenetic point of view. To clarify the functional neural features underlying learning mechanisms, general explanations about plasticity have been widely provided. Nevertheless, although motor learning has been carefully investigated, many questions remain, to which often ambiguous and inconsistent answers are given. In particular, the distinction between implicit and explicit learning is occasionally equivocal and could generate misunderstandings when applied to the concept of movement. From a classical point of view, implicit learning refers to procedural and unconsciousness knowledge, whereas explicit learning refers to declarative and conscious knowledge. More recently, Keele et al. (11) proposed a model in which the dichotomy inherent to the distinction between implicit and explicit learning modalities refers to the involvement of attentional resources in the learning process (11). In their perspective, implicit learning requires a low-level of attentional demand, while explicit learning refers to the need for substantially more attentional resources, thus implying a continuous rather than dichotomous nature of the two learning modalities, and indeed, previous data revealed an overlap of these two, both in terms of neural processing and of involved cerebral networks (9). This concept concurs well with the so-called “hodotopic” organization of the central nervous system in parallel, dynamic, and interactive networks: thus, human functions, such as learning and memory, have to be re-thought beyond their modular and rigid conceptualization. Otherwise, it does not imply a loss in their functional specificity, which remains absolutely crucial from both research and applicative perspectives (9, 60).

The existence of an interactive overlap among different learning processes could be considered as a point of strength in human motor behavior. Moreover, from a neurorehabilitation point of view, the distinction between implicit and explicit strategies to be applied in the clinical context, and the comprehension of their role in motor learning and adaption are pivotal.

The acquisition and improvement of motor skills are one of the central goals in neurorehabilitation. However, circumstances, in which motor learning strategies are applied may differ substantially from patient to patient and depend on the clinical situation (61). Actually, there is no consensus regarding the “correct” application of the implicit and the explicit motor learning strategies in neurorehabilitation. An explicit motor learning approach, based on volition and attention, makes use of explicit verbal and/or visual instructions, strategies to be applied to reach a given goal, cues, and feedback. These rules are not addressable for implicit motor learning, given its proper nature: implicit learners may be able to free-up attentional resources to perform given tasks (62). Going beyond this distinction, it is important to understand that the application of motor learning strategies has to be set with respect to the functional state of the patients (63–65). Therefore, while implicit learning may be particularly beneficial for those patients who suffer from cognitive impairments (e.g., amnesia or aphasic), others may particularly benefit from receiving explicit explanations (e.g., in patients with Parkinson's disease).

To bridge the gap in the field, we have designed an experimental study that aimed at evaluating whether a non-invasive stimulation of the cerebellum affects performances related to explicit motor learning and adaptation. Due to the cross-sectional design of the study, we expect to be able to distinguish between the encoding and retrieval phases.

The cerebellum is a unique hub in the central nervous system, as it is phylogenetically developed for receiving and integrating both afferent and efferent inputs from almost the entire brain. Its structural organization promotes the integration of motor and non-motor aspects of behavior and their subsequent predictive computation, which is required for motor learning and motor control (66, 67). The role of the cerebellum in implicit learning has been extensively studied (49, 68), whereas little is known about its possible role in explicit learning (3, 69).

We expect to confirm the previously described findings (49), which showed improvement of implicit motor adaptation and subsequent re-adaptation following cerebellar iTBS (49). Furthermore, we anticipate that iTBS will positively affect all phases of explicit motor learning and adaptation by enhancing the predictive computation in favor of voluntary-engaged attentional strategies. Conversely, cerebellar cTBS could induce the opposite effect.

In the future, results from this study could be translated in the clinical setting for implementing and extending the use of NIBS in neurorehabilitation. In this perspective, the effectiveness of rehabilitation strategies to be applied in all the phases of the re-learning process could be hopefully empowered.

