Motor learning results from activity in a complex cortico-subcortical network, which entails different areas, such as the motor cortex, the prefrontal cortex, the parietal cortex, the basal ganglia, and the cerebellum (1, 4, 13). Although the imaging data have so far not provided definitive evidence of a specific role of each area in the different phases of learning, consistent results indicate a crucial role of the cerebellum for motor sequence learning and motor adaptation, as it subserves error correction of on-going actions and contributes to sensorimotor integration (13–15).

Knowledge about motor learning has relevant, practical, and applicative values in neurorehabilitation, as principles of motor learning can be applied to the methodologies designed to promote clinical recovery in neurologically affected patients (16–18). The non-invasive brain stimulation techniques (NIBS), eventually combined with standard physical therapy (19–23), were shown to be effective in fostering and maximizing motor learning resources (24–29).

Augmentation of motor learning through the application of NIBS has previously been attempted in implicit motor learning paradigms (30–32). Indeed, modulation of the cerebellum was considered effective and easy, given the role this area plays in motor learning (33, 34).

The effect of a non-invasive cerebellar stimulation has been tested in various motor tasks (30, 35–44). A cerebellar repetitive transcranial magnetic stimulation (rTMS) induces long-lasting changes in the excitability of the contralateral primary motor cortex (M1) (45, 46) and may interfere with the cerebellar cognitive functions (47). Excitatory and inhibitory rTMS can also be administered in the form of TBS with the same efficacy and safety, but with the great advantage of requiring much shorter application times and lower stimulation intensities (48).

Recently, Koch et al. (49) demonstrated acceleration of motor adaptation following excitatory intermittent TBS (iTBS), applied to the right cerebellar hemisphere. Furthermore, TMS combined with electroencephalogram (TMS-EEG) revealed relevant changes of cortical activity in the interconnected motor networks induced by cerebellar iTBS (49). Block and Celnik (50) previously demonstrated enhancement of motor learning after anodal transcranial direct current stimulation (tDCS) of the right cerebellum but no effect in inter-manual transfer.

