#### Theta Burst Stimulation

Group 1 (G1) will receive cerebellar iTBS before the session 1 and sham stimulation before the session 2; group 2 (G2) will receive cerebellar sham stimulation before the session 1 and cerebellar iTBS before the session 2; group 3 (G3) will receive cerebellar cTBS before the session 1 and sham stimulation before the session 2; group 4 (G4) will receive cerebellar sham stimulation before the session 1 and cerebellar cTBS before the session 2 (as shown in Figure 1).

Theta burst stimulation protocols will be carried out using a Magstim Super Rapid stimulator (Magstim Company, Whitland, UK) and a 70 mm figure-of-eight coil. TBS stimulation intensity will be set at 80% of the active motor threshold (AMT), defined as the lowest intensity which evoked at least five out of 10 MEPs with an amplitude > 200 μV peak-to-peak amplitude in the first dorsal interosseous (FDI) muscle during 10% of maximum voluntary contraction (56). This stimulation intensity was previously shown to produce plastic changes in the contralateral primary motor cortex (M1) (57). The iTBS protocol consists of a 2 s train of TBS repeated 20 times, every 10 s for a total of 190 s (48). The cTBS protocol consists of three-pulse bursts at 50 Hz repeated every 200 ms for 40 s (48). TBS will be applied over the lateral cerebellum, i.e., 1 cm inferior and 3 cm lateral to the inion (57). A cerebellar TBS is expected to modulate neural activity in the interconnected contralateral motor and parietal areas (57, 58). The coil will be positioned tangentially to the scalp, with the handle pointing superiorly; for sham TBS, it will be angled away so that no current was induced in the brain (59). Sham TBS will be delivered with an intermittent pattern in G1 and G2 and with continuous pattern in G3 and G4.

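### At delayed recall and re-adaptation, G1 vs G2 and G3 vs G4 compare stimulation before session 1 with stimulation before session 2, so encoding and retrieval effects cannot be separated against sham

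*Protocol article*

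**What the plan says.** The Theta Burst Stimulation section fixes four sequences. G1 is stimulated with iTBS first and has sham second. G2 has the opposite order: "group 2 (G2) will receive cerebellar sham stimulation before the session 1 and cerebellar iTBS before the session 2". The cTBS pair mirrors this, with G3 active first and G4 active second.

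No group has sham before both sessions. The same section gives sham an intermittent pattern in G1 and G2 and a continuous pattern in G3 and G4.

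Under Behavioral Tasks, a single 12-item sequence serves motor sequence learning (MSL), adaptation (AD), DR and RA. MSL and AD belong to session 1, DR and RA to session 2. For DR, "participants repeated the AD task after 45 min and following another stimulation protocol".

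Behavioral Task Analysis names four group comparisons (G1 vs G2, G3 vs G4, G1 vs G3, G2 vs G4) across the four tasks, in a two-way repeated measures ANOVA.

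The Discussion then expects: "Due to the cross-sectional design of the study, we expect to be able to distinguish between the encoding and retrieval phases". It also anticipates a benefit of iTBS in every phase and possibly the opposite for cTBS.

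**The concern.** Session 2 re-tests what was learned in session 1, on the same day and with the same material. Everyone who is on sham in session 2 was actively stimulated before learning the sequence. The sham side of G1 vs G2 and of G3 vs G4 is therefore not an untreated reference at DR and RA, because it carries whatever is left of the session-1 effect.

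At stake is what may be concluded about retrieval. Under the authors' own expectation for iTBS, the retained session-1 benefit in G1 and the session-2 benefit in G2 have the same sign, so they pull against each other in the difference. A small difference at DR or RA could be read as no retrieval effect, and a large one as a pure stimulation effect. Neither reading is warranted without an assumption about persistence, and the article states none.

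**Working it through.** The article gives no effect size, alpha or sample-size calculation for this point, so there is no figure to reproduce. The question is what the group means can identify.

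**Session-2 means.** At DR (and likewise at RA) let m be the mean under sham in both sessions, e the session-1 effect still present, and r the effect of session-2 stimulation, with i for iTBS and c for cTBS. Positive values mean better performance. From the four sequences:

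| Group | Session 1 / session 2 | Mean at DR |
|---|---|---|
| G1 | iTBS / sham | m + e_i |
| G2 | sham / iTBS | m + r_i |
| G3 | cTBS / sham | m + e_c |
| G4 | sham / cTBS | m + r_c |

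There are four means for five unknowns. The design matrix has rank 4, and none of m, e_i, e_c, r_i, r_c is estimable alone. Adding the session-1 means brings in three more parameters (session-1 sham level and two session-1 effects). The joint rank is 7 of 8: the session-1 effects are estimable, while e and r still are not.

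**What the named comparisons estimate at DR or RA.**

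- G1 − G2 = e_i − r_i (mixed)
- G3 − G4 = e_c − r_c (mixed)
- G1 − G3 = e_i − e_c (both sham in session 2: persisting encoding effect, iTBS versus cTBS)
- G2 − G4 = r_i − r_c (both sham in session 1: retrieval effect, iTBS versus cTBS)

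The last two do not mix phases, but they have no sham reference and compare groups with different sham patterns.

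**Change from AD to DR.** Let s_i be the session-1 effect at AD, where G1 − G2 = s_i is a clean contrast with sham. If practice and delay act equally and additively in both groups, they cancel in the difference of changes:

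change in G2 − change in G1 = r_i − (e_i − s_i) = r_i + s_i − e_i

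The DR difference taken the same way round is G2 − G1 = r_i − e_i. The change contrast equals r_i if e_i = s_i (full persistence), and the DR difference equals r_i if e_i = 0 (full decay). For e_i between 0 and s_i the two enclose r_i, and the gap between them is s_i.

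**Illustration.** Assumed, not in the article: s_i = r_i = 0.8 SD.

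| Session-1 effect retained | e_i | DR difference, G2 − G1 | Change contrast |
|---|---|---|---|
| 0% | 0 | 0.8 − 0 = 0.8 | 0.8 + 0.8 − 0 = 1.6 |
| 50% | 0.4 | 0.8 − 0.4 = 0.4 | 0.8 + 0.8 − 0.4 = 1.2 |
| 100% | 0.8 | 0.8 − 0.8 = 0 | 0.8 + 0.8 − 0.8 = 0.8 |

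In every row the true retrieval effect, 0.8, lies between the last two columns or equals one of them. With 10 per group (40 divided equally, an assumption) and a two-sided 5% t-test, a DR-only comparison would reject in about 40%, 14% and 5% of trials in the three rows. The 5% simply reflects setting e_i = r_i.

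For the full-persistence row, assume also a correlation of 0.6 between AD and DR. The SD of the change is √(2 × (1 − 0.6)) = 0.894, the standardised change contrast is 0.8 / 0.894 = 0.894, and the change contrast rejects in about 47% of trials.

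The change contrast is not safe alone either. With no retrieval effect (r_i = 0) and full decay (e_i = 0) it equals 0 + 0.8 − 0 = 0.8.

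**The case against.** The strongest defence is that the Discussion sentence never says against sham, and that the design does deliver part of what it promises. That stands. Effects on initial learning and adaptation are cleanly compared with sham at MSL and AD. At DR and RA, G1 vs G3 and G2 vs G4 separate the two phases for iTBS relative to cTBS. The sentence needs restricting, not deleting.

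A reader might also infer that the retained and retrieval effects cancel and the trial would therefore conclude that retrieval is unaffected. The article does not support that. It plans a repeated measures ANOVA on group and task and states no DR-only decision rule. The group-by-task interaction ordinarily included in such a model carries the change contrast, which under full persistence equals the retrieval effect. What remains is that this contrast absorbs any decay of the session-1 effect, so it does not identify retrieval without an assumption.

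It is tempting to cite the Introduction as proof of carry-over, since it says that cerebellar rTMS "induces long-lasting changes in the excitability of the contralateral primary motor cortex". That sentence concerns cortical excitability and gives no duration. It does not show that a behavioural effect of TBS outlasts a 45-minute break. The firmer ground is that DR and RA re-test the sequence learned in session 1. How much of a session-1 gain is retained is unknown.

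Finally, the numbers in the illustration are assumed. The estimability result does not depend on them.

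**Conclusion.** The point holds for G1 vs G2 and G3 vs G4 at DR and RA. There the planned comparison estimates retained session-1 effect minus session-2 effect, and the expectation of separating encoding from retrieval is not met against sham unless persistence is assumed. This follows from the four sequences and the single motor sequence alone. An analysis plan that is not shown cannot supply a sham-sham reference.

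The size depends on retention. With equal effects in both sessions, the DR difference is 1.0, 0.5 or 0 times the retrieval effect for 0%, 50% or 100% retention, so it could be near zero despite a real effect. With unequal effects it is r − e, of either sign. The bracketing result further assumes additive practice and delay effects common to both groups, and decay between none and full.

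The term cross-sectional is also wrong for a two-session design with repeated measurements on the same people.

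**What to change.** - In the Discussion, limit the claim to active-versus-sham effects in session 1 (MSL, AD) and iTBS-versus-cTBS effects in session 2: G1 vs G3 for persisting encoding effects and G2 vs G4 for retrieval. Note that the sham patterns differ in the latter comparisons.
- Label G1 vs G2 and G3 vs G4 at DR and RA as stimulated before session 1 versus before session 2, not as stimulation versus sham.
- Report the between-group difference in AD-to-DR change beside the DR difference. State that the first equals the retrieval effect under full persistence and the second under full decay, so that together they bracket it for decay in between.
- Do not adjust for end-of-AD performance to recover the retrieval effect. It is measured after stimulation, and conditioning on it does not restore identification.
- Replace cross-sectional with a two-session, repeated-measures sequence design.

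The cost is a narrower conclusion for DR and RA and some rewording; no new data are needed. A sham-sham sequence would make all five quantities estimable (rank 5 of 5), but it is a trade-off and not part of this correction. The Population section describes the 40 participants as already enrolled, and five equal groups would have 40 / 5 = 8 each. At two-sided 5% and 80% power, using (1.96 + 0.84) × √(2/n), the detectable pairwise difference would rise from about 1.25 SD with 10 per group to about 1.40 SD with 8.
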